#### Process measures

Process measures will identify areas of attention for IF procedures and implementation support. These include qualitative interview matrices, log of IF activities at each site (e.g., meetings and learning collaborative attendance, rollout of promotional material, dates of academic detailing, etc.), change rulers to assess readiness and preparedness to provide PrIMO (delivered alongside all site staff participant assessments), and focus groups as part of the formative evaluation. Approximately two focus groups will be conducted (one with supervisors/leadership and one with supervisees/staff) at each site by the external facilitators. Focus groups will be audio recorded to ensure the accuracy of information conveyed to the investigators and clinic teams implementing the model. Demographic information will be collected to characterize participating staff. Focus group findings are not considered outcome measures, and therefore all learning they generate will inform the process for implementation at each site.

## Analysis

The primary outcome measure will result in a binary variable that represents whether the site completes Stage 6 (model launch) of the SIC. The summary statistics for this outcome will include the number and percentage (%) of sites reaching Stage 6. SIC variables of duration (length of time in days) and proportion scores will be treated as continuous variables and summarized using descriptive statistics [median, mean, standard deviation (SD), range and quartiles] and comparisons will be made between study sites to understand the most optimal patterns of implementing PrIMO. Although the sample of four feasibility sites is insufficient to draw statistical conclusions, activity completion and site implementation behavior will be observed across the pre-implementation and implementation phases.

Combining quantitative site staff and patient perspectives of model acceptability with qualitative interview, model fidelity, and cost data will serve to contextualize and better understand the acceptability of the PrIMO model at the primary care clinics engaged in the study. The secondary outcomes (implementing PrIMO model acceptability and impact) will result in quantitative and qualitative endpoints. Quantitative analyses at the site level will be purely descriptive in nature and precision estimates for key secondary outcomes at the staff, provider and patient level will be conducted. Categorical outcomes collected as Likert scale items will be presented as ordinal variables (as appropriate). Responses with two non-ordinal levels such as Yes/No or Complete/Incomplete, will be analyzed as binary variables using summary statistics such as frequency/counts and proportions. Analyses for quantitative secondary outcomes will use the same descriptive statistics described in the primary outcome analysis and will be presented by timepoint. Corresponding 95% confidence intervals will be provided for key secondary outcomes. This is an exploratory study and will not require multiplicity adjustments for multiple testing. Any exploratory analyses that use hypothesis testing will use an alpha level of 0.05 for evaluating statistical significance.

Qualitative interviews will undergo direct content analysis [67] to identify themes and subthemes found across participant subgroups. Analysis of these outcomes will be conducted at individual data collection time points (site summary matrices populated synchronously by time point) and at study completion (time-ordered, sequential site summary matrices populated diachronously).

Interviewers will use individual interview forms (i.e., ‘templated summaries’ [68]) as the analytic tools for the cross-sectional analyses, which will be populated as soon as possible following each interview. Interviewers will embed relevant text segments from interview transcripts generated by Zoom into interview forms that have been pre-coded by CFIR constructs. A secondary analyst (i.e., member of the team who did not conduct the interview) will review completed interview forms for thoroughness and accuracy. Once all interviews have been conducted at a site for a given data collection timepoint, a rapid cross-sectional analysis will be conducted for each site (site staff and patients), generating site summary matrices by timepoint (a random subset will be reviewed by secondary analysts to ensure trustworthiness)**.** Mixed method analysis, or the systematic integration of qualitative and quantitative measures of acceptability for the purposes of triangulation (seeking convergence/divergence of both types of outcome data) and expansion (seeking a more comprehensive understanding of acceptability of PrIMO and its implementation) [69, 70] will occur at study completion once all data have been collected.

The study hypothesizes that it will be feasible to implement the PrIMO model (complete SIC Stage 6) using the IF implementation approach, and that it will be acceptable, will positively impact patient outcomes one year post-model launch (e.g., increased MOUD treatment retention, medication regimen adherence, service utilization for co-morbid conditions, and decreased substance use including opioid abstinence), and will increase each clinic’s capacity for caring for patients with MOUD (e.g., increased number of patients, number of prescribers, and rate of patients per prescriber).

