#### Implementation Facilitation strategy

Implementation Facilitation (IF) is the comprehensive strategy incorporating a bundle of interconnected implementation activities that will be used to support and enable clinical sites to implement the PrIMO model. The IF strategy utilized in this study was manualized by Kirchner and colleagues [34] and used by study investigators in previous studies [36–39]. In this study, IF relies on a collaborative partnership between local site champions (provider and pharmacist) who have in-depth knowledge of the organization (e.g., norms, culture, change agents) and external facilitators who serve as content experts on the innovation (PrIMO model developers, addiction and psychiatry expertise, implementation researchers). Champions serve as leaders of practice change within the clinic, forging relationships with local partners, tailoring the model to site-specific conditions, and building enthusiasm. They work closely with external facilitators and serve as key liaisons between the two teams. External facilitators work with local partners and provider and pharmacist champions to conduct a formative evaluation, develop, and refine clinical procedures or resources, perform academic detailing and staff education, lead a learning collaborative offering continuing medical education units, and facilitate performance monitoring and feedback. Elements of the IF approach are outlined in Table 2.

**Table 2 Tab2:** Implementation Facilitation (IF) activities

IF activities	IF activity description
Engagement of local partners	Local partner engagement involves creating an atmosphere that is open, non-critical, and goal oriented. Engagement of key partners will take place at the administrative, provider, pharmacist, pharmacy technician, and patient levels
Formative evaluation	Formative evaluation is an implementation assessment approach designed to identify influences on the development, progress, and effectiveness of implementation efforts related to the PrIMO model and use these data to tailor, refine, and monitor the implementation of the model. Approximately two focus groups per site will be conducted with additional individual meetings with local partners. Change rulers will provide ongoing evaluation of readiness and preparedness, gathered electronically

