#### Design

This is a longitudinal mixed-methods implementation study that combines qualitative and quantitative methods using survey and EHR data. Qualitative and quantitative outcomes will be measured across sites, site staff participants (e.g., providers, pharmacists, pharmacy technicians, and administrators), and patient participants in MOUD to assess the extent of implementation and barriers and facilitators to implementation and sustainability.

Site staff must be 18 years of age or older, speak and read English fluently, employed by the participating clinic, and were exposed to the PrIMO model through an introductory email sent by the Site Principal Investigator to all staff (this email contained a letter from the model developers and a graphic explaining the six Core Components of the PrIMO model). They will be recruited via posters, emails, or word-of-mouth and after providing informed written consent will complete quantitative surveys at approximately 3 months pre-PrIMO launch, at launch, 3 months post-launch, 6 months post-launch, 9 months post-launch, and 12 months post-launch. Site staff will be invited to participate in qualitative interviews at 3 months pre-launch, at launch, 6 months post-launch, and 12 months post-launch timepoints. Site staff will have the opportunity to participate at each timepoint to best capture the model’s acceptability.

Patients must be 18 years of age or older, receiving MOUD from a provider at the participating clinic, and exposed to the model for at least 2 weeks (to best protect study data from contamination related to the clinic’s MOUD procedures prior to PrIMO launch). Patients will be recruited from the participating clinics via posters, flyers, and word-of-mouth; they complete baseline, 3-month post-baseline, and 6-month post-baseline surveys and will be invited to participate in interviews at each timepoint. Patient enrollment will last for approximately 6 months.

EHR data, including aggregate treatment outcomes from all patients on MOUD at the clinic, and administrative data, including data on provider capacity, MOUD prescribing, and staff training, will inform impact and be collected for a period of 12 months pre- and post-model launch.

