#### Acceptability

Site staff and patient participants will complete longitudinal quantitative surveys and qualitative interviews (for a subset of participants) at various timepoints surrounding model launch (see Table 4) to assess acceptability. Site staff and patient participants will follow the same procedures for screening and enrollment: at the index (staff) or baseline (patients) visit, RCs will obtain verbal consent and conduct a brief screening to confirm study eligibility specific to the participant group (including an assessment of age, prisoner status, clinic role for site staff candidates, and length of exposure to the PrIMO model for patient candidates) before consenting potential participants. Site staff and patient participants will be compensated with $100 gift cards for each completed survey (up to six for site staff and three for patients), and $100 gift cards for the subset of participants that complete qualitative interviews (up to four for site staff and three for patients), though one site’s current union contract prohibits compensation for site staff. Staff and patient participants will self-complete quantitative survey assessments. After completing their first survey timepoint, participants will be invited to participate in qualitative interviews until participant maximums or saturation is reached. Participants will meet with research staff electronically (via Zoom) to review all significant elements of the qualitative interviews via an IRB-approved verbal consent. All study materials will be approved by the single IRB (sIRB, BRANY).

**Table 4 Tab4:** Participant assessments

		3 months pre-PrIMO launch	Launch	3 months post-launch	6 months post-launch	9 months post-launch	12 months post-launch
Site staff participants							
The applied mental health research dissemination and implementation (AMHR) measure	Participant perceptions of model adoption, acceptability, appropriateness, feasibility, reach/access, organizational climate, leadership in implementing, and general leadership skills of the clinic	✓	✓	✓	✓	✓	✓
Modified clinical sustainability assessment tool (CSAT)	Participant perceptions of the model’s clinical sustainability		✓	✓	✓	✓	✓
The medical conditions regard scale (MCRS)	Biases, emotions, and expectations of chronic medical conditions, including Type2 diabetes, depressive disorder, HIV/AIDS, alcohol use disorder, stimulant use disorder, and opioid use disorder	✓	✓	✓	✓	✓	✓

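### Repeated staff and patient surveys are summarised only by timepoint, so a change in who answered can be read as a change in views, and the within-person information goes unused

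*Protocol article*

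**What the plan says.** The Design section calls the study longitudinal. Table 4 schedules staff surveys at six timepoints, from three months before launch to twelve months after, and patient surveys at the patient's own baseline, three months and six months. In the text after Table 4, Beliefs on MOUD, the change rulers and the SU-SMS are described as following stigma or readiness over time.

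For recruitment, the section on acceptability under Study population describes staff and patients as convenience samples. The Design section says: "Site staff will have the opportunity to participate at each timepoint". Staff are paid per survey, except that at one site a labour agreement "prohibits compensation for site staff".

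The Analysis section then states the method: "Analyses for quantitative secondary outcomes will use the same descriptive statistics described in the primary outcome analysis and will be presented by timepoint". The primary-outcome statistics it refers to are "summarized using descriptive statistics [median, mean, standard deviation (SD), range and quartiles" and, for the binary outcome, counts and percentages. On uncertainty it says that "precision estimates for key secondary outcomes at the staff, provider and patient level will be conducted", and adds: "Corresponding 95% confidence intervals will be provided for key secondary outcomes". Site-level quantitative analyses are to be descriptive only. No within-person change, repeated-measures analysis or rule for changing respondents is named.

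**The concern.** A series of by-timepoint summaries answers one question well: how acceptable the model was to those who answered at that moment. It answers a different question badly: whether people's views changed. The survey text names that second question for three measures, and readers will ask it of every scale that is repeated.

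Two things go wrong if change is read from the tables. First, the respondents at two timepoints need not be the same people. Staff who leave, stop answering or (if late entry is allowed, which the article does not spell out) join later alter the mean even if nobody changes their mind. The Discussion itself names staff shortage as a real-world problem that will affect results. Patients are a cohort anchored to their own baseline, so for them the problem is limited to dropout. Second, a reader who compares two separately reported means treats them as independent samples and gets a less precise answer than the linked data can give.

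The article's own handling of the interviews shows the gap. They are analysed at each timepoint and again in time-ordered matrices at study completion. The surveys get only the first of these, although the two sources are to be triangulated.

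**Working it through.** **No figure to reproduce.** The article states no sample-size calculation, interval width, within-person correlation, attrition or turnover. The numbers below are illustrations on assumed values.

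**Group sizes (section on acceptability under Study population).**
- Staff per site: lower end 5 + 2 + 2 + 2 = 11, upper end 20 + 6 + 10 + 10 = 46. Over four sites, 44 to 184.
- Patients per site: 12 to 40. Over four sites, 48 to 160.
- Pharmacists number only 2 to 6 per site, so one person entering or leaving matters within a role.

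**Shift in a timepoint mean from turnover alone (staff).** Shift = share replaced × gap between leavers and joiners.
- 10% replaced, gap 0.3 SD: 0.10 × 0.3 = 0.03 SD.
- 20% replaced, gap 0.5 SD: 0.20 × 0.5 = 0.10 SD.
- 40% replaced, gap 0.8 SD: 0.40 × 0.8 = 0.32 SD.

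**Shift from loss without replacement (patients, or staff who stop answering).** If a share d is lost and leavers differ from stayers by g, the mean among those remaining moves by d × g.
- 10% lost, gap 0.3 SD: 0.03 SD.
- 30% lost, gap 0.8 SD: 0.30 × 0.8 = 0.24 SD.

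**Precision left unused.** For equal variances and complete pairs, SE of paired change ÷ SE from two independent samples = √(1 − ρ).

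| Assumed ρ | Ratio of SEs | Unpaired width ÷ paired width |
|---|---|---|
| 0.3 | √0.7 = 0.84 | 1.20 |
| 0.5 | √0.5 = 0.71 | 1.41 |
| 0.7 | √0.3 = 0.55 | 1.83 |

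**What matching costs.** With a fraction f of n respondents matched, the paired SE is SD × √[2(1 − ρ)/(fn)]. The SE that treats the two timepoints as independent is SD × √(2/n). They are equal at f = 1 − ρ. Restricting to matched respondents therefore still gives the smaller SE when more than 70%, 50% or 30% are matched, at ρ = 0.3, 0.5 and 0.7. A repeated-measures model keeps the unmatched respondents as well.

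**Which measures have which first survey (Table 4).** AMHR, MCRS, Beliefs on MOUD and the change rulers start three months before launch. The modified CSAT and the ICBS start at launch. The champions complete the ICBS as raters of other staff.

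**The case against.** The strongest reply is that the study is exploratory and these outcomes are secondary. The acceptability hypothesis is about a level, and a summary with its interval at each timepoint answers it. The stated hypotheses of increase or decrease concern health-record outcomes and site capacity. An analysis plan that is not shown may add paired analyses, and nothing in the article excludes them. This stands in part. It is why the by-timepoint tables should stay and why this is an improvement rather than a serious defect. It does not answer the measures that the article itself says are followed over time.

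One further objection is fair. Non-payment at one site applies throughout, so it may lower participation there but does not by itself shift the mix between timepoints.

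A reader might also infer stronger claims that the documents do not support:

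- **That pooled intervals ignore site.** The article does not say whether the 95% intervals are pooled or given by site, or how they are computed. An article commonly leaves that to the full plan. A design effect for pooled results would matter only when generalising beyond these sites, and the Analysis section itself concedes the limit: "Although the sample of four feasibility sites is insufficient to draw statistical conclusions".
- **That the pairing is lost, or that intervals for change are too wide.** The same consented people are followed, so the linked data remain available. No interval for change is stated.
- **That one of only two pharmacists at Sites A and C is the champion.** Table 3 lists two pharmacists under pharmacy characteristics, but for Site C it also mentions a clinical pharmacist without saying whether that person is one of the two. What does hold is that champions, whose role includes "tailoring the model to site-specific conditions, and building enthusiasm", complete at least the ICBS among the staff assessments. A check without them is reasonable.

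**Conclusion.** The concern holds in a limited form. Followed as written, the survey analysis mixes change in respondents with change in views and leaves the within-person information unused, in a study that calls itself longitudinal. The point is stronger for staff than for patients.

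Its size cannot be fixed from the article. Under the assumed turnover and gaps, the artificial shift for staff runs from negligible (0.03 SD) to large enough to be mistaken for an effect (0.32 SD). Under assumed correlations of 0.3 to 0.7, an unpaired comparison is 1.20 to 1.83 times as wide as a paired one. The feasibility outcome is not touched, and neither is the level of acceptability among respondents at any one timepoint.

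**What to change.** 1. Keep the by-timepoint tables as the summary of the level of acceptability.
2. For Beliefs on MOUD, the change rulers, the SU-SMS and the other repeated scales, add within-person change from each person's first survey on that scale. Use either the paired change among respondents common to both timepoints, or a repeated-measures model with a random effect for person and fixed effects for site and, for staff, role. Use an ordinal version for Likert items.
3. Report the number of matched respondents for each comparison, and respondents over eligible staff by site and role at each timepoint.
4. Show estimates by site. If a pooled 95% interval is given, stratify it by site and state that it describes these four sites only.
5. Repeat the staff summaries without the champions as a sensitivity check. This does not apply to the ICBS, where the champions are the raters.
6. State that the within-person analysis does not remove bias from non-response driven by views that were not observed. If sceptical staff stop answering for such reasons, neither the paired summary nor the model corrects it.

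The cost is analysis wording and modest programming, with no new data on participants' views. The downside is smaller numbers in the paired summaries, which the matched counts make visible.

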## Discussion and next steps

Through a longitudinal, mixed-methods approach, we will assess the feasibility, acceptability, and impact of implementing this model of care for OUD in four diverse primary care settings. As this study will examine implementation in situ, real-world problems faced by each clinic (e.g., a healthcare staffing shortage) will directly impact results and be translatable to other clinics that may want to implement PrIMO. These data may be used to inform how PrIMO may be implemented in primary care settings to help providers treat OUD, increase access to and retention in MOUD, enhance the role of pharmacists, and reduce stigmatization of MOUD (for providers and patients) with the goal of decreasing the morbidity and mortality of OUD in the US.

As the opioid overdose epidemic continues to claim lives at an alarming rate, multidisciplinary approaches to support both patients receiving MOUD and prescribers are needed. Leveraging relationships between primary care clinics, pharmacists and pharmacies might improve access and outcomes. As the role of pharmacists continues to expand to support chronic disease management for many conditions, there is tremendous opportunity to engage pharmacists in integrated care teams to provide MOUD. The PrIMO model of care offers a patient-centered approach to MOUD that integrates the pharmacist as a key member of the care team. Stigma related to OUD is a pervasive barrier in health systems that inhibits wider implementation of MOUD treatment and scalability [71]. Lessons learned in this implementation feasibility study may inform recommendations to increase knowledge of OUD as a chronic disease that includes safe and effective medication treatment, enhances trust and rapport among care team members to increase confidence and mitigate burnout, and bolsters the relationship between providers and patients to help promote desired treatment outcomes.

One of the novel aspects of this study is that its design will allow us to share practical learnings as they emerge. Presentations to clinic systems, pharmacy groups, substance use treatment authorities, training programs, and other venues can widely disseminate lessons learned from this study in nontraditional ways. These dissemination efforts could have a novel impact on systems throughout the US that could help to rapidly scale this model. These efforts could also inform policies related to access to care, including those related to reimbursement strategies to make models like PrIMO easier for clinics to implement and sustain.

